**Methods:**

The objective of this explorative, longitudinal intervention study is to provide an in-depth understanding of the psycho-social background of 30 children aged 6–12 years living in institutional or family-centered foster care. Data will be collected at three time points: before, after and 12 months after participating in the newly developed group intervention, which intends to address the particular needs of children of drug abusing parents living in foster care in the latency period. The study is conducted at the Faculty of Psychology of the University of Vienna in collaboration with the Association “Dialogue” (Verein Dialog). The treatment duration spans 5 months, during which two specifically trained psychotherapists conduct 10 group sessions for children and three group sessions for foster caregivers. All statistical analyses will consider the type of data available. Therefore, the primary outcome of the study will be assessed via the Friedman test due to the ordinal dependent variable as it is the non-parametric alternative to the one-way ANOVA for repeated measures. In addition, the Mann–Whitney U test is used to compare differences between two independent groups (children living in institutional foster care vs. family foster care). To assess potential correlations regarding the child and caregivers’ capacity to mentalize, Spearman correlations (ρ) are conducted. To examine the secondary outcome, apart from the methods previously outlined, we will also utilize qualitative thematic analysis.

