### Participants

2.2

In the study 30 children living in foster care (institutional or foster home) and their actual main foster caregiver will be included (*N* = 60).

Children’s inclusion criteria for participation are: (1) age between 6 and 12 years, (2) stable mental health status (e.g., no psychotic state), (3) living in foster care for at least 6 months. A minimum of time in a stable and persistent placement needs to be considered to assure the children’s ability to reorganize their internal world and behavioral outcomes (Cassibba et al., 2023). Caregiver’s inclusion criteria are (1) child lives in the same household and (2) 18 years of age or older. Children are excluded from the study if presenting neurological, cognitive, and/or psychiatric problems, and/or difficulties reported by their caregiver.

Children in middle childhood, aged between 6 and 12, are very common as primary target of mentalization-based treatments. However, middle childhood has received only limited attention regarding the ability to mentalize (Midgley et al., 2021).

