### Statistical plan and data analysis

2.6

Sociodemographic data will be used to characterize the sample and to provide an in-depth look into the participant’s psycho-social background. Frequencies and means are derived for demographic variables.

Thresholds for the measures will be used to describe each case, and to provide descriptive statistics, such as frequencies, mean and standard variation (SPSS 27.0), for each group: caregivers, children living in foster families and children living in institutional foster care.

Analyses on quantitative data will be conducted using the statistical software SPSS (IBM, Version 27.0).

All statistical analyses will consider the type of data available. Therefore, the primary outcome of the study will be assessed via the Friedman test as it is the non-parametric alternative to the one-way ANOVA with repeated measures, to compare the changes in reflective functioning scores between the pre-intervention, post-intervention, and one-year follow-up assessments, with the group (family foster care vs. residential programs) as a between-subjects factor and the time of assessment (pre, post, follow-up) as a within-subjects factor. In addition, the Mann–Whitney U test is used to compare differences between two independent groups (foster family and institutional foster care). To assess potential correlations regarding the child and caregivers’ capacity to mentalize, Spearman correlations (ρ) are conducted.

For the secondary outcome variables we choose a mixed-method approach for data analysis. Qualitative data from the “Patte-noir” will be processed via qualitative thematic analysis (Braun and Clarke, 2006). To provide an in-depth understanding of the psycho-social background of foster children and their foster caregiver, taking into account the caregivers’ social competences, their attitudes to drugs and drug addiction and the children’s mental state, quantitative methods, equal to the ones for the primary outcome variables, will be used.

This mixed-method approach was chosen to obtain different and multiple perspectives to validate the results and to build a comprehensive understanding.

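### The primary analysis gives the Friedman test a between-subjects factor it cannot hold, and the Mann–Whitney test that could compare care types has no stated input

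*Protocol article*

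**What the plan says.** Under Statistical plan and data analysis (2.6), the article states that "the primary outcome of the study will be assessed via the Friedman test", which it presents as the rank counterpart of a one-way repeated-measures ANOVA. The same sentence gives the purpose as comparing changes in RF between pre-intervention, post-intervention and one-year follow-up. It then sets out two factors: care type, "with the group (family foster care vs. residential programs) as a between-subjects factor", and "the time of assessment (pre, post, follow-up) as a within-subjects factor".

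The next sentence adds that "the Mann–Whitney U test is used to compare differences between two independent groups (foster family and institutional foster care").

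The abstract names the Friedman test for the ordinal primary outcome because "it is the non-parametric alternative to the one-way ANOVA for repeated measures". It gives the test no between-subjects factor. It repeats the Mann–Whitney comparison of care types: "the Mann–Whitney U test is used to compare differences between two independent groups (children living in institutional foster care vs. family foster care").

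Neither place says whether the Mann–Whitney test is applied to RF at T1, T2 or T3, or to changes in RF. Section 2.6 also says that the quantitative secondary outcomes will be analysed with the same methods as the primary outcome.

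**The concern.** Section 2.6 describes a two-factor mixed design, one factor between children and one within, but names a test that holds only the within-child factor. The sentence itself places Friedman beside the one-way repeated-measures ANOVA, so its two halves disagree. An analyst following it has to improvise, either by pooling all children and ignoring care type, or by running Friedman separately in each care type and comparing p-values, which is not a test of a difference.

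At stake is whether RF develops differently in family and residential care. The only other tool in the plan for this is the Mann–Whitney test. Its input decides what it tests, and that input is open, so it could be chosen after the data are seen. Because the methods carry over, the quantitative secondary outcomes inherit the same ambiguity.

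**Working it through.** The article gives no alpha, effect size or power for this analysis, so there is no planned figure to reproduce. The check has a structural part, free of assumptions about the data, and a simulated part that is only illustrative.

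**Inputs from the article.** n = 30 children (Participants: "In the study 30 children living in foster care (institutional or foster home) and their actual main foster caregiver will be included"); k = 3 visits; two care types; RF scored from −1 to 9 and treated as ordinal.

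**1. A level difference between care types.** Without ties, the Friedman statistic is Q = 12/(n·k·(k+1)) × ΣR_j² − 3n(k+1), where R_j is the sum over children of the within-child ranks at visit j. For n = 30 and k = 3, 12/360 = 1/30 and 3 × 30 × 4 = 360, so Q = ΣR_j²/30 − 360. Care type does not appear. Adding a constant to all three scores of a child leaves that child's ranks, and hence Q, unchanged. In a simulated data set, adding 3 points to every score in one care group gave chi-square 0.18, p = 0.914, both before and after.

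**2. A difference in course.** Take an extreme constructed case: 15 children in one care type rise at every visit (ranks 1, 2, 3) and 15 in the other fall at every visit (ranks 3, 2, 1).
- Pooled: each R_j = 15×1 + 15×3 = 60 (or 30×2 = 60), so Q = 3 × 3600/30 − 360 = 0.
- One care type alone (n = 15): R = 15, 30, 45; ΣR_j² = 225 + 900 + 2025 = 3150; Q = 12/180 × 3150 − 180 = 30, the maximum n(k − 1) = 15 × 2.

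The pooled statistic is zero although each group has the strongest possible time effect. Mann–Whitney on T2−T1 would separate the two groups completely.

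**3. Dependence on the Mann–Whitney input.** Assumed here: two-sided alpha 0.05 per test, between-child and within-child SD 1 RF point each, rounded scores, no dropout, splits 15/15 and 18/12, 4000 runs. Rejection rates over both splits:

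| Scenario | Friedman, pooled | Mann–Whitney on score at T2 or T3 | Mann–Whitney on change from T1 |
|---|---|---|---|
| Constant difference 1.5 | 4–5% | 73–77% | 4–5% |
| Opposite trends ±0.75 | 3–5% | 74–77% | 72–74% |
| Opposite trends ±1.0 | 2–5% | 93–95% | 92–94% |

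Scores at a visit therefore respond to a constant difference and to a difference in course alike; changes respond only to the latter.

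**4. Smaller effects.** Assumed here: between-child SD 1.0, visit SD 0.8, baseline mean 3, rounded scores, 3000 runs. Average change is the mean of T2 and T3 minus T1; the last column is a two-sample t-test on it.

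| Split; changes | Friedman, pooled | MW, score at T2 or T3 | MW, T2−T1 | MW, average change | t-test, average change |
|---|---|---|---|---|---|
| 15/15; +0.5/−0.5 | 4% | 47–48% | 56% | 69% | 71% |
| 12/18; +0.8/0 | 23% | 33–34% | 37% | 48% | 51% |
| 12/18; +0.5/−0.3 | 4% | 33–34% | 39% | 49% | 51% |

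Moving the Mann–Whitney input from a single-visit score to average change shifts rejection by about 14 to 21 points. Under the same assumptions a common rise of 0.5 or 0.8 points in all children is detected by pooled Friedman in 56% and 93% of runs.

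**The case against.** The strongest reply is that care type is tested. A reader of the Friedman sentence alone might infer that a difference between care types would be missed outright. The documents do not support that: section 2.6 and the abstract both plan a Mann–Whitney comparison of the care types. Applied to average change it nearly matches a t-test on the same quantity (69% against 71%, 48% against 51%, 49% against 51%). Nor can one assert that the Mann–Whitney test compares levels only, since the text leaves its input open. This stands, and it limits the consequence to one that depends on the input chosen.

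A reader might also infer that the primary analysis fails altogether. It does not. The first aim, under Aims, is the development of children's mentalization over three time points and does not name care type. Pooled Friedman serves that aim, and the abstract's account of it is coherent. The very low Friedman figures also need care types moving in opposite directions, whereas the article expects RF to rise, and setting a pooled time test beside a care-type contrast partly just shows that they answer different questions.

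Finally, the study is exploratory and uncontrolled, and an article may leave the choice of input to a fuller plan. That excuses brevity, but not a sentence that joins a test to a factor it cannot hold.

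**Conclusion.** The concern holds in limited form. The primary analysis in section 2.6 cannot be run as written. That follows from the construction of the Friedman test and rests on no assumption about the data. The sentence also differs from the abstract, which gives the test no care-type factor, and the mismatch carries over to the quantitative secondary outcomes.

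A difference in course between care types could be missed, depending on an input that the text does not fix. How often is not known for this trial: the percentages rest on assumed SDs, effects, baseline mean and care-type splits, and the article supplies none of these for its sample. With 30 children and care type not randomised, the comparison stays exploratory however it is analysed.

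**What to change.** In section 2.6, choose one of two routes.

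(a) Name a method that holds one between-subjects and one within-subjects factor for an ordinal outcome: a rank-based ANOVA-type statistic for longitudinal data, or an ordinal mixed model with visit, care type and visit × care type. Bring the abstract into line.

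(b) Remove the between-subjects clause from the Friedman sentence, keep Friedman for the pooled time effect, and state that Mann–Whitney U compares the T2−T1 and T3−T1 changes between care types, reported with an estimate and 95% CI. The abstract's Friedman sentence can then stay.

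Either route keeps the authors' choice to treat RF as ordinal. A Gaussian mixed model is not needed to repair the fault. State that the choice also applies to the quantitative secondary outcomes, and label the care-type comparison as exploratory.

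The cost is rewording and a little analysis work, with no new data. Route (b) is the smaller change, but it gives two separate comparisons of change rather than one interaction test, and each single change is less sensitive than the average where a shift is sustained (56% against 69% in the 15/15 scenario above).

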### Aims

2.1

The first aim of this study is to explore the development longitudinally of the children’s mentalization ability at three measure time points: before, after and 12 months after attending a newly developed group MBT-intervention. It is an adapted version of Midgley et al. (2017). Mentalization-Based Treatment for Children (MBT-C), which addresses the particular needs of children of substance using parents, who live in foster care during middle childhood, integrating the psycho-social background of children living in foster care. Second, we will explore the mentalization capacity of the caregivers, their attitudes on drugs and drug addiction, and their social skills (e.g., social orientation and reflexibility) with regard to the impact on the children’s mentalization at the beginning of the intervention to better understand whether it influence the development of mentalization over time.

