## Discussion

3

This study uses the concept of mentalization to identify affective and cognitive abilities of the caregiver-child dyad with the aim of compensating deficits on both sides with psychological-psychotherapeutic strategy. On the foster caregivers’ side, social structures and their anchoring in the social environment are addressed. Their prejudices are pointed out and questioned with the aim of providing suitable measures for change. Cassidy (2018) highlights that a foster caregiver of a traumatized child should be able to consistently empathize with the child, understanding that the child’s challenging behaviors may be a result from the child’s past experiences of abuse and neglect. As a further consequence, the child may be able to develop more secure and less disorganized attachment representations. On the children’s side, the emotional and affective background is illuminated, which at the same time reveals the risks for their future emotional, cognitive and social development. According to Suchman et al. (2020), cited in Paris et al. (2023), to the implementation of mentalization based approaches in research and practice of SUD patients treatment is still missing.

Initial findings from our research indicate that certain institutional foster caregivers exhibit low levels of mentalization capacity. Consequently, in collaboration with the Institute for Drug Prevention of the Office of Addiction and Drug Policy of Vienna, we will start in the near future the development for a mentalization-focused training program for institutional foster caregivers. The primary aims will be the enhancement of their reflective functioning, defined as the ability to mentalize, and to heighten sensitivity in interpersonal communication with children experiencing complex PTSD. The comprehensive training regimen will span several days of training sessions, supplemented by at least one mandatory reflection meeting within the initial year. The evaluation of the program’s effectiveness will rely on pre- and post-training measures of participants’ reflective functioning, utilizing an adapted version of the Reflective Functioning Questionnaire (RFQ-8). The detailed methodology and further findings will be disseminated in a forthcoming publication. The continued availability of this training program is an example for the successful transfer of results from a scientific study into practice to actually provide support to the sensitive target group.

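### For the over-time part of Aim 2, the only caregiver-child analysis named is a bivariate Spearman correlation with no time point, change score or adjustment

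*Protocol article*

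**What the plan says.** Aim 2 (section 2.1, Aims) has two parts. It begins "we will explore the mentalization capacity of the caregivers, their attitudes on drugs and drug addiction, and their social skills", and looks at these "with regard to the impact on the children’s mentalization at the beginning of the intervention". That is a cross-sectional question at T1. It then continues "to better understand whether it influence the development of mentalization over time", which is a question about the child's later course.

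Section 2.6 (Statistical plan and data analysis) names these quantitative methods:

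- A Friedman test of RF over the three assessments, with care type named as a between-subjects factor.
- A care-type comparison: "the Mann–Whitney U test is used to compare differences between two independent groups (foster family and institutional foster care").
- For the dyad: "To assess potential correlations regarding the child and caregivers’ capacity to mentalize, Spearman correlations (ρ) are conducted".
- For caregiver social competences and drug attitudes, the same quantitative methods as for the primary outcome.

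The sample is fixed in section 2.2: "In the study 30 children living in foster care (institutional or foster home) and their actual main foster caregiver will be included".

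**The concern.** The second part of Aim 2 needs an analysis that relates a caregiver characteristic at the start to what happens to the child's RF afterwards. Of the methods in section 2.6, only the Spearman correlation puts a caregiver measure and a child measure together. It is bivariate, the section does not say which visit or score enters it, and nothing is held constant. The same method carries over to drug attitudes and social skills.

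If caregiver and child RF are already associated at T1, and child RF is fairly stable, caregiver RF will correlate with child RF at T2 and T3 even when the caregiver adds nothing to development. Change scores do not cure this. They bring in regression to the mean and produce a spurious correlation of the opposite sign. A difference between care types in both members of the dyad can act in the same way.

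The Discussion says that findings will feed research questions for further studies, and that a caregiver training programme is about to be developed. A correlation read as caregiver influence could misdirect both.

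**Working it through.** **Inputs.** From the documents: 30 dyads (section 2.2), RF scored from -1 to 9 (section 2.3.1), and assessments at T1, T2 and T3 (section 2.4). The article gives no power, alpha or effect-size figure, so there is no stated figure to reproduce. Assumed: two-sided alpha 0.05, T1-T2 stability s = 0.6, baseline dyad correlation r = 0.4 or 0.5, and an age effect of 0.3 SD. A baseline dyad link is plausible on the article's own account, since the Introduction cites work in which parental RF predicted children's mentalization.

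**Which method contains what**

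| Method in section 2.6 | Caregiver variable | Child's later course |
|---|---|---|
| Friedman | none | yes |
| Mann-Whitney by care type | care type only, no caregiver characteristic | not stated |
| Spearman, child and caregiver RF | yes | not stated |

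No row relates a caregiver characteristic to the child's development given where the child started.

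**Expected correlation when the caregiver has no effect on development** (standardised scores)

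- Caregiver T1 RF with follow-up child RF: r × s. This is 0.4 × 0.6 = 0.24 and 0.5 × 0.6 = 0.30.
- Caregiver T1 RF with change in child RF: r(s − 1)/√(2(1 − s)). This is 0.4 × (−0.4)/√0.8 = −0.18 and 0.5 × (−0.4)/√0.8 = −0.22.

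Neither is zero, although the true effect on development is.

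**Rejection rates under that null.** Simulation of 30 dyads, 4,000 runs, scores rounded to the RF scale. The adjusted analysis is a partial rank correlation given T1 RF, age and care type.

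| Baseline dyad r | Care-type effect on caregiver and on follow-up child RF | Spearman, follow-up | Spearman, change | Adjusted |
|---|---|---|---|---|
| 0 | none | 5.2% | 5.0% | 4.9% |
| 0.4 | none | 21.8% | 13.2% | 5.5% |
| 0.5 | none | 30.2% | 17.4% | 5.5% |
| 0.4 | 0.8 SD | 43.7% | 4.3% | 4.2% |
| 0 | 0.8 SD | 11.3% | 11.7% | 4.9% |

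A simpler simulation without an age term, adjusting for T1 RF and care type only, gives up to 20% on change scores and about 6% after adjustment. In the fourth row the two biases happen to cancel on change scores, which nobody could count on.

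**Care type alone, no link within care type.** Assumed: 12 and 18 dyads in the two care types.

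| Gap, caregiver / child (RF points) | SD, caregiver / child | Mean pooled rho | Significant |
|---|---|---|---|
| 1.5 / 0.8 to 1.0 | about 1.2 / 1.0 | 0.18 to 0.23 | about 17-23% |
| 1.5 / 0.8 to 1.0 | 1.5 / 1.5 | 0.11 to 0.13 | 9-11% |
| 1.5 / 0.8 to 1.0 | 2.0 / 1.5 | 0.09 to 0.11 | 8-10% |
| 1.0 / 0.5 | 1.5 / 1.2 | 0.06 | 6% |

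The direction is constant, but the size runs from about 6% to 23% and depends on gaps and SDs that the article does not give.

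**Price of adjusting.** The smallest rho detectable with 80% power is tanh((1.96 + 0.842) × √(1.06/(n − 3 − k))), where k is the number of covariates. With n = 30 and k = 0, tanh(2.802 × √(1.06/27)) = 0.50. With k = 3, tanh(2.802 × √(1.06/24)) = 0.53.

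**The case against.** The strongest reply is that the study is explorative, has 30 dyads, disclaims generalisation, and chose rank methods because the outcome is ordinal. An article may also leave the choice of visit and score to a fuller plan. That stands as a reason to keep any repair small and rank-based where possible. It does not remove the point, because the article names a method for the dyad question and that method, on any of the scores it could use, does not isolate development.

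Three stronger readings are tempting, and the documents do not support them.

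- A reader might infer that Aim 2 as a whole goes unanswered. It does not: the first part concerns the start of the intervention, and Spearman at T1 describes that.
- A reader might infer that the plan relies only on unadjusted two-variable tests and ignores care type. Section 2.6 also plans a Friedman test over time, names care type as a factor there, and uses it as the Mann-Whitney grouping. Care type is absent only as an adjustment in the caregiver-child correlation. The Mann-Whitney comparison itself is not part of Aim 2.
- A reader might take the Discussion's remark that "certain institutional foster caregivers exhibit low levels of mentalization capacity" as evidence of confounding by care type. It makes no comparison with foster parents and gives no size, so confounding by care type remains a possibility.

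The article also does not say that follow-up rather than change scores will be used, so both are shown above.

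**Conclusion.** The point holds for the over-time part of Aim 2. The method named there does not fit the question asked. Under no true caregiver effect on development it would give a significant result in about 22-30% of trials on follow-up scores and 13-20% on change scores, against about 6% once T1 RF and care type are held constant. These rates rest on assumed stability of 0.6 and an assumed baseline dyad correlation of 0.4 to 0.5. If there is no baseline dyad association and no care-type effect, the unadjusted test is sound at about 5%. The care-type contribution is plausible, but its size is not established. Because the study is explorative and the data are already planned, this is worth correcting before analysis, but it does not undermine the trial.

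**What to change.** In section 2.6, split the Aim 2 analysis in two.

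1. Baseline part: Spearman correlations of child RF with each caregiver measure at T1, partialled for care type and labelled as description.
2. Over-time part: for child RF at T2 and at T3, an analysis on each caregiver T1 measure (RF, the two social-skills subscales, drug attitudes), entered one at a time and adjusted for the child's T1 RF, age and care type. A partial rank correlation respects the ordinal score. A small regression or mixed model is an alternative if the authors accept treating the score as interval. Report each as an exploratory estimate with a 95% CI.

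If the authors prefer not to add this, limit Aim 2 to the baseline description and drop the wording on influence over time.

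No new data are needed: T1 RF and care type are recorded, and age is an inclusion criterion ("age between 6 and 12 years"). The cost is a few model terms on 30 children and therefore wide intervals. The smallest partial rho detectable with 80% power is about 0.53, against about 0.50 unadjusted, so adjustment itself takes little from a study that is imprecise either way.
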